### 5.2 Exclusion criteria

- 1) Patients who plan to initiate maintenance dialysis or have a kidney transplant within 24 weeks after registration
- 2) Patients with malignant tumors, blood disorders, or obvious hemorrhagic lesions
- 3) Patients with hypersensitivity to ESA components or to ESA
- 4) Pregnant women, lactating women, patients who may be pregnant, or patients wishing to become pregnant during the research period
- 5) Patients participating in other clinical trials
- 6) Other patients deemed inappropriate for this research by the lead principal physician or study physician

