## 8.2 Discontinuation criteria for each patient and its handling

The necessary items are recorded up to the traceable time point in the case report form and the “discontinuation report form” in the following patients.

- 1) When a patient has died.
- 2) When a patient cannot be contacted and becomes untraceable.

However, if the transfer destination is known, the patient will be tracked by obtaining data from the transfer destination facility or by calling, and tracing will be continued.

- 3) When a patient requests discontinuation from research participation (patient information prior to discontinuation can be used).
- 4) When a patient has requested consent withdrawal (patient information after registration cannot be used).

- 5) When the lead principal physician or study physician deemed that research participation should be discontinued.

Patients in whom any of the following are applicable are not considered discontinued, with normal observation period inspections continued to the extent possible, and information up to the time point of 96 weeks collected.

- 1) Patients who transitioned to renal replacement therapy (dialysis, kidney transplantation).
- 2) When a patient has requested discontinuation of darbepoetin alfa use.
- 3) When the lead principal physician or study physician deemed that darbepoetin alfa use should be discontinued due to adverse events, etc.

The lead principal physician or study physician will make efforts to provide the best possible treatment to the patient even after discontinuation of research participation.

If it was determined after registration that a patient did not meet the eligibility criteria at the time of registration, then this will be considered “ineligible after registration,” and research participation will be concluded for the patient. Adverse event information up to 30 days after the decision to complete participation will be reported for patients in whom darbepoetin alfa was administered even once.

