|     |                                                             | Blood transfusion amount                                                                                                                                                                                                                                              |                                                                                                                                                                           |                                                                                                                                                                                                                                                                                                                                                                                                                                |
| 9   | Development of factors that affect anemia                   | Malignant tumors, hemorrhagic lesions, collagen disease and rheumatic disease, immunosuppressant or steroid use (apply “2. Concomitant drug usage status” data correspondingly), other myelosuppressive factors (details)
Note) refer to attachment for definition |                                                                                                                                                                           |                                                                                                                                                                                                                                                                                                                                                                                                                                |

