#### 13.2 Analysis set

The following groups are defined as the analysis sets. The acceptance or rejection of individual patients in each group is determined prior to the fixing of the data as needed. The main analysis set for efficacy evaluation is set as the “efficacy analysis set,” but a similar efficacy analysis is implemented for “ACS.”

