### 13.2.2 Efficacy analysis set

The group excluding the following patients from the safety set is defined as the efficacy analysis set.

- Those who were ineligible after registration
- Those who discontinued darbepoetin alfa administration within 12 weeks after the start of treatment
- Those who do not have a single DA administration record 12 weeks after the start of treatment
- Hb concentration measurements are not obtained at the start of treatment and at 12 weeks

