### 13.3.1 Renal function deterioration, CVD event investigation

A proportional hazards model that includes the following covariates is applied, and the factors that affect event occurrence are investigated. Covariates are added or decreased as required for the investigation of the model. Hb concentration values at each measurement time point up to 24 weeks instead of week 12 of administration are also investigated. The presence of diabetic complications, arteriosclerosis, and chronic inflammation should also be considered as stratification factors. These analyses are used to investigate the prediction equation for event occurrence from the covariates.

- Age; sex; weight; eGFR, serum albumin, hemoglobin concentration, high-sensitive CRP, NT-pro BNP, folic acid, vitamin B12, serum iron, serum ferritin, and TSAT 12 weeks after the start of treatment; the presence of diabetic complications, arteriosclerosis, chronic inflammation, malignant tumor complications, hemorrhagic lesion complications, collagen disease and rheumatic disease complications, concomitant immunosuppressant or steroid use, and other myelosuppressive factors; and the darbepoetin alfa administered dose (total administered dose, administered dose 12 weeks after the start of treatment).

Next, the cut-off values of each ERI are gradually increased from the minimum value to the maximum

value; a time-dependent ROC curve of the survival time data with censoring is created, and the AUC is compared. If the cut-off value is set from the ROC curves of each obtained ERI, then these are divided into two groups at the cut-off value, Kaplan-Meier plots are created, and the annual event occurrence rate (human-year method) and 95% confidence intervals are estimated. The cut-off values of the ERIs may also be investigated using the cross-validation method, if considered useful.

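### Ineligibility can be declared at any time after registration and ends outcome follow-up, so removal from the efficacy set can depend on the response under study

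*Protocol*

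**What the plan says.** Protocol Section 8.2 deals with patients found ineligible after enrollment. The trigger is "If it was determined after registration that a patient did not meet the eligibility criteria at the time of registration". The consequence is that "research participation will be concluded for the patient". For patients who received at least one dose, "Adverse event information up to 30 days after the decision to complete participation will be reported". The section names no deadline, no standard of evidence and no decision-maker.

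Section 13.2.2 lists, among the patients taken out of the efficacy analysis set, "Those who were ineligible after registration". Section 13.2 makes this the main set for the efficacy evaluation and adds: "The acceptance or rejection of individual patients in each group is determined prior to the fixing of the data as needed". The compliance set in Section 13.2.3 is a subset of it. The safety set (Section 13.2.1) keeps all treated patients.

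Section 5.2 excludes malignant tumors, blood disorders and obvious hemorrhagic lesions. It also has an open criterion of physician judgement. Section 2 names bleeding, hematopoietic tumors and blood disorders among the causes of low ESA response.

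Section 10.1.3, item 9, records factors affecting anemia that develop on study, beginning "Malignant tumors, hemorrhagic lesions, collagen disease and rheumatic disease". Section 13.3.1 puts "malignant tumor complications, hemorrhagic lesion complications" among the covariates of the proportional hazards model.

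**The concern.** The study asks how patients with a low response to darbepoetin alfa fare. Some conditions that cause a low response are also exclusion criteria. A poor hemoglobin response is a natural reason to look for them. If a tumor or blood disorder is then found and judged to have been present at registration, Section 8.2 ends participation and Section 13.2.2 removes the patient. A good responder with the same unrecognized condition is less likely to be investigated and so stays in. The test concerns baseline status, but whether it is ever applied can depend on the exposure being studied.

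Two things are at stake: a main analysis set selected partly on response, and permanent loss of renal and CVD outcomes after the decision. The second cannot be left to the statistical analysis plan, because no analysis can recover outcomes that were never collected.

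**Working it through.** **The protocol's own figure.** Its only calculation is the event count in Section 13.1: 2,000 × 2 × 0.131 = 524, and 524 ± 1.96 × √524 gives 479.1 to 568.9, against the stated 480 to 568. It reproduces, and this point does not depend on it.

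**One patient, two routes.** Take a patient with a malignancy present but unrecognized at registration and found on study.

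| Provision | Treatment of this patient |
|---|---|
| 5.2 with 8.2 | Criteria unmet at registration: participation ends |
| 13.2.2 | Removed from the main analysis set |
| 10.1.3, item 9 | Recorded as a factor affecting anemia, observation continues |
| 13.3.1 | Kept in the model, with malignancy as a covariate |

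Nothing says when the first two rows apply and when the last two do, so two sites could handle identical patients in opposite ways. Section 10.1.2 also lists existing malignancy, including blood diseases, among the baseline complications to be recorded. The passages must be reconciled.

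**Why removal may differ by response.** The chance of removal is roughly the prevalence of the hidden condition times the chance of finding it. Section 2 gives a reason for higher prevalence among low responders. More frequent detection among them is my inference about work-up; the protocol gives no data on it.

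**When the decision falls.** Both endpoint clocks start at treatment week 12 (Sections 12.1.1 and 12.1.2). A removal before then selects on response but not on endpoint events. A later removal can be made with events already known, because nothing requires otherwise.

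**What is lost.** In Section 8.2 only withdrawal of consent makes post-registration data unusable, so data up to the ineligibility decision remain available. After it, only the 30 days of adverse events are provided for. Section 10.1.4 describes the simultaneous survey as covering all patients, but does not say that this includes patients whose participation has ended.

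**Conditional size.** The protocol gives no expected number of such patients, so these inputs are assumptions:
- 1%, 3% or 5% of the 2,000 are removed: 20, 60 or 100 patients.
- Three quarters of them come from the poorest-response quarter of 500: 15, 45 or 75.
- The removed share of that quarter is therefore s = 0.03, 0.09 or 0.15.
- h is the event rate of the removed patients relative to those who stay.

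With base rate r, the full quarter has rate r × (1 − s) + r × h × s, and the analyzed quarter has rate r. So analyzed/full = 1 / (1 + s(h − 1)), and the base rate cancels.

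| s | h = 0.5 | h = 2 | h = 3 |
|---|---|---|---|
| 0.03 | 1/0.985 = 1.015 | 1/1.03 = 0.971 | 1/1.06 = 0.943 |
| 0.09 | 1/0.955 = 1.047 | 1/1.09 = 0.917 | 1/1.18 = 0.847 |
| 0.15 | 1/0.925 = 1.081 | 1/1.15 = 0.870 | 1/1.30 = 0.769 |

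With h of 2 to 3 the quarter's rate is understated by 2.9% to 23.1%. With h = 0.5 it is overstated by 1.5% to 8.1%.

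**The case against.** The strongest reply is that the rule asks only whether criteria were met at registration. Eligibility is determined and recorded then, so a later reversal has to contradict a dated record. A reader might infer that the protocol lets patients be removed because of their course. The text does not say that. This part of the reply stands, and the point is confined to how a baseline failure comes to be discovered.

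A reader might also infer that early dialysis events can be struck out. Treatment may start 0 to 8 weeks after registration and the renal clock starts 12 weeks later, so the 24-week horizon overlaps endpoint time by 24 − (12 to 20) = 4 to 12 weeks. But the exclusion is worded "Patients who plan to initiate maintenance dialysis or have a kidney transplant within 24 weeks after registration", which is a plan and not the event. Section 8.2 expressly keeps patients who move to dialysis or transplantation and follows them to 96 weeks. Relabelling such a case as previously planned would be misuse of the rule.

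Third, only obvious hemorrhagic lesions are excluded. A bleeding source found only on later work-up was arguably not obvious at registration, which leaves mainly malignancy and blood disorder.

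Fourth, settling analysis sets before data fixing is ordinary practice, and an analysis plan could add blinded case review. That is fair for set membership. It does not answer the end of outcome collection, which Section 8.2 itself fixes.

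Finally, keeping patients whose anemia proves to have a pre-existing non-renal cause widens the population studied. That is a real choice, but the item 9 records and the covariates show that the protocol already means to study such factors.

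**Conclusion.** The point holds in a limited form. As written, the protocol permits exclusion from the main analysis set that can depend on response. No evidence date, time limit or blinding is attached, and renal and CVD outcome collection stops at the decision. It also leaves unresolved whether a malignancy found on study is a ground for exclusion or a covariate.

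The 3% to 23% range is an illustration, not an estimate. Its frequency, concentration and relative rates are all assumed, and the direction is open too. Cancer death is not an endpoint, and the protocol gives no reason to expect a particular renal or CVD rate in the removed patients. It would also go too far to say that no sensitivity analysis is possible: data up to the decision can be used, though such an analysis would have to censor patients at a date that may be linked to their response.

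The study is exploratory and the number of patients affected may be small. The change is still worth making, because lost follow-up cannot be repaired afterward.

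**What to change.** Four changes:

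1. In Sections 8.2 and 13.2.2, limit post-registration ineligibility to violations verifiable from information dated on or before registration. Name who decides, and have the decision made without sight of hemoglobin response or events.
2. State that conditions first discovered later are handled as factors affecting anemia under Section 10.1.3, item 9, and through the Section 13.3.1 covariates, with the patient kept in the efficacy set. This reconciles those passages with Sections 5.2 and 8.2.
3. Continue renal, CVD and survival outcome collection to the simultaneous survey for every treated patient who has not withdrawn consent, including those ruled ineligible, and say so in Section 10.1.4.
4. Add a sensitivity analysis that includes the treated patients ruled ineligible.

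The cost is an amendment to a few sections, a few more outcome forms, and slightly more heterogeneity in the efficacy set, which the listed covariates partly address.

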### 8.3 Recommended concomitant treatment

#### 8.3.1 Iron replenishment therapy

The presence of iron is important for the development of the improvement effects of darbepoetin alfa on renal anemia, and iron formulations should be administered with reference to the latest information, such as the guidelines of academic societies when iron efficiency occurs.

**Table Iron administration criteria of each guideline**

| Guideline                                        | Iron formulation administration criteria                                                                                                                                                                        |
|--------------------------------------------------|-----------------------------------------------------------------------------------------------------------------------------------------------------------------------------------------------------------------|
| 2006
KDOQI guideline                          | Replenish so as to maintain ferritin value $> 100$ ng/mL and TSAT $> 20\%$ . However, there is little evidence for administering iron formulations at ferritin value $> 500$ ng/mL.                             |
| 2008
Japanese Society for
Dialysis Therapy | Replenish iron during ESA therapy when TSAT is less than $20\%$ and ferritin value is less than $100$ ng/mL. *1                                                                                      |
| 2012
CKD clinical
guideline                | Replenish iron during ESA therapy when TSAT is less than $20\%$ and ferritin value is less than $100$ ng/mL. Do not intentionally increase when ferritin value is above $250$ ng/mL.                            |
| 2012
KDIGO guideline                          | Hb increases or ESA decreases are desirable in renal anemia patients who are not using iron formulations, and iron formulations should be administered if TSAT $\leq 30\%$ and ferritin value $\leq 500$ ng/mL. |

\*1 The upper limits of TSAT and ferritin values are not specified.

(reference: “evidence-based CKD clinical guideline 2013”).

### 8.3.2 Treatment where concomitant use is prohibited

The administration of drugs of the same type or with the same efficacy as darbepoetin alfa (e.g., epoetin beta pegol, epoetin alfa, epoetin beta) is prohibited during the observation period.

If prohibited concomitant use is applied during the observation period, the reason is recorded in the case report form, and research participation is continued.

## 8.4 Post-treatment

No particular provisions are made regarding treatment after the discontinuation/completion of this research.

The lead principal physician or study physician will make efforts to provide appropriate and optimal treatments according to guidelines even after the discontinuation/completion of the research or its early discontinuation (see “20. Research completion and early discontinuation”).

## 9. Evaluation and reporting of adverse events

### 9.1 Definition

#### 9.1.1 Definition of adverse event

An adverse event refers to any unfavorable medical event (e.g., subjective and objective symptoms, abnormal laboratory test values) observed during or within 30 days after the discontinuation or termination of administration of darbepoetin alfa, regardless of a causal relationship with darbepoetin alfa.

#### 9.1.2 Definition of serious adverse events

The following are referred to as serious adverse events.

- (1) Death
- (2) Injury
- (3) Risk of death
- (4) Risk of injury
- (5) Hospitalization or its extension due to treatment
- (6) Serious events relating to above-mentioned (1)–(5) (other medically important conditions)
- (7) Congenital disorders or abnormalities in later generations

#### 9.1.3 Definition of outcome

The outcomes of adverse events in this study were determined based on the following definitions:

|                   |                                                                                                                                                     |
|-------------------|-----------------------------------------------------------------------------------------------------------------------------------------------------|
| Recovery          | When the adverse event has disappeared, and the patient has recovered to their state prior to the occurrence of the adverse event                   |
| Remission         | When the adverse event has almost disappeared, and the patient has returned to a state similar to that prior to the occurrence of the adverse event |
| Non-recovery      | When the adverse event has not disappeared, and the patient is in a state similar to that during the occurrence of the adverse event                |
| Recovery but with | When the adverse event has disappeared, but the patient has sequelae                                                                                |

|          |                                                                                                                                                                              |
|----------|------------------------------------------------------------------------------------------------------------------------------------------------------------------------------|
| sequelae |                                                                                                                                                                              |
| Death    | When the lead principal physician or study physician determine that there is an association between the adverse event and death, or when its possibility cannot be ruled out |
| Unknown  | When there is no information, and it is unknown                                                                                                                              |

## 9.2 Evaluation and reporting of adverse events in this study

All adverse events that occurred during or within 30 days after discontinuation or termination of administration of darbepoetin alfa, all adverse events that occurred by the end of the simultaneous outcome survey are subject to evaluation in this study.

Serious adverse events, as specified in “9.1.2 Definition of serious adverse events” are reported according to “9.4 Emergency reporting of adverse events and subsequent responses” and “Appendix 2 Reporting and response manual when serious adverse event occurs.”

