### 8.1 Recommended renal anemia treatment

This research is an observational study, so the following treatment methods are recommended.

Among CKD patients diagnosed with renal anemia, those for whom ESA administration was deemed necessary will receive the expected DA according to the package insert and observed for 96 weeks from the start of treatment (see Section 8.1.1 for target values of renal anemia treatment).

The participants in this study will include patients who did not receive ESA within 12 weeks prior to registration, and inspections in this research will be implemented following consent acquisition. DA administration will begin within eight weeks after registration.

The final administration of DA during the observation period will be performed immediately before 96 weeks after the start of treatment, but treatment will be continued as necessary after the completion of the observation period.

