#### 9.4 Emergency reporting of serious adverse events and subsequent responses

##### 9.4.1 Adverse events which must be reported

Adverse events that must be reported include all serious adverse events specified in “9.1.2 Definition of serious adverse events,” that occur from the start of darbepoetin alfa administration to within 30 days after its completion or discontinuation.

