### 10.1.3 Observation period (from start of treatment-96 weeks later)

Report the information closest to each survey point among the inspection results included in the permissible range.

Start of treatment: day of blood tests; urine tests can be performed up to -4 weeks, blood test HbA1c up to -8 weeks)

Weeks 2, 4, 6, 8, 10, 12, and 16 after the start of treatment:  $\pm 1$  week

Weeks 24, 36, 48, 60, 72, 84, 96 after the start of treatment:  $\pm 6$  weeks

|        |                                             |                                             |                                                                                                                                                                                     |                                                                                                                                     |
|--------|---------------------------------------------|---------------------------------------------|-------------------------------------------------------------------------------------------------------------------------------------------------------------------------------------|-------------------------------------------------------------------------------------------------------------------------------------|
| 1
* | Darbepoetin alfa administration status      | Administration date                         | yyyy/mm/dd                                                                                                                                                                          |                                                                                                                                     |
|        |                                             | Administration route                        | Intravenous administration, subcutaneous administration, other (details)                                                                                                            |                                                                                                                                     |

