#### 10.1.4 Simultaneous outcome survey (96 weeks from the start of the final registered patient)

A simultaneous outcome survey will be conducted for all patients 96 weeks after the start of the final registered patient.

|        |                                                   |                                            |                                                                                                                                            |                                                                                                                                                                                                                                                                                                                                                                                                                                |
|--------|---------------------------------------------------|--------------------------------------------|--------------------------------------------------------------------------------------------------------------------------------------------|--------------------------------------------------------------------------------------------------------------------------------------------------------------------------------------------------------------------------------------------------------------------------------------------------------------------------------------------------------------------------------------------------------------------------------|
| 1      | Outcome                                           | Outcome status                             | Survival
Death (cause of death: fatal CVD event, other (details))
Unknown (reason)                                                   |                                                                                                                                                                                                                                                                                                                                                                                                                                |

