#### 12.2.2 Safety evaluation

The presence of adverse events and contents are evaluated for all adverse events occurring after the administration of darbepoetin alfa. MedDRA/J is used as a replacement dictionary for adverse events. The latest version at the time of analysis is used for the MedDRA/J. Those where the association with darbepoetin alfa is deemed “present” are defined as adverse drug reactions.

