### 13.3.3 Safety evaluation

The number of occurrences is tabulated for all adverse events and adverse drug reactions. The tabulation of frequency according to content is performed according to the system organ class (SOC) and preferred term (PT) of MedDRA/J.

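### Sections 9.1.1, 9.2 and 12.2.2 do not give one adverse event window, and after a patient's week 96 no listed item records whether darbepoetin continued

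*Protocol*

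**What the plan says.** **The windows.**
- Protocol 9.1.1 defines an adverse event as an unfavorable medical event "observed during or within 30 days after the discontinuation or termination of administration of darbepoetin alfa", whatever its cause.
- Protocol 9.2 names that same window and then, after a comma and with no conjunction, states that "all adverse events that occurred by the end of the simultaneous outcome survey are subject to evaluation in this study".
- Protocol 12.2.2, the secondary safety endpoint, evaluates "all adverse events occurring after the administration of darbepoetin alfa". It gives no end point.
- Protocol 13.3.3: "The number of occurrences is tabulated for all adverse events and adverse drug reactions". There is no split by time on or off drug.

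**The data collected.**
- Section 10.1.3 lists darbepoetin date, route and dose from the start of treatment to week 96, each entry covering the time since the previous survey point. It also lists an occurrence date for each adverse event, and the name of and reason for any other ESA.
- Section 8.1 says of darbepoetin after week 96 that "treatment will be continued as necessary after the completion of the observation period".
- Section 10.1.4: "A simultaneous outcome survey will be conducted for all patients 96 weeks after the start of the final registered patient". Its items are outcome, event and adverse event (with date and causal relationship). No darbepoetin item appears.
- Section 14.1 extends the event and adverse event forms to the simultaneous survey. It attaches no such extension to the darbepoetin administration form.

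**The concern.** An event three months after the last darbepoetin dose is not an adverse event under 9.1.1. It can be one under 9.2 and 12.2.2. Such patients will exist: under 8.2, those who stop darbepoetin or start renal replacement therapy stay under observation, and under 8.3.2 so do those given another ESA. Sites and analysts could therefore apply different windows to the same patient.

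The second problem is one of data rather than wording. Whichever window is chosen, applying a 30-day rule needs the date of the last dose. Every patient who starts before the last one has follow-up beyond their own week 96, and adverse events are still collected then. Exposure is not. An analysis plan can choose how to tabulate, but it cannot recover dosing dates that were never recorded. What is at stake is the interpretation of a named secondary endpoint: how many of the tabulated events occurred under darbepoetin.

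**Working it through.** The plan gives no figure on this point, so there is none to reproduce. The check has two textual steps and one illustration of size.

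**1. Can 9.2 be read so that the sections agree?**

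| Reading of 9.2 | Consequence |
|---|---|
| Union: the 30-day window, and also everything up to the survey | Evaluates events that 9.1.1 says are not adverse events |
| Cap: events meeting 9.1.1, cut off at the survey | Agrees with 9.1.1, but needs the last-dose date for all follow-up up to the survey |

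The first reading contradicts the definition. The second does not, but it cannot be applied once dosing is no longer recorded.

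**2. Where can events be classed?**

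| Period | Darbepoetin record | Event date | Can it be classed? |
|---|---|---|---|
| Start to week 96 | Yes, dated (10.1.3) | Yes | Yes: on drug, within 30 days, or later |
| Up to 30 days after the last recorded dose | Last dose known | Yes | Yes, inside the window |
| Later, patient still treated at week 96 | None listed (10.1.4, 14.1) | Yes | No |

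**3. How much follow-up is in the last row?** Section 11.2 gives the end of registration (March 31, 2016) but ties its start to an approval date that is not stated, so accrual length is an assumption.

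Assumptions: uniform accrual over A months, no attrition, survey 96 weeks after the last patient's start, and last recorded dose at about week 96 (8.1 places the final dose of the observation period just before it).

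- Accrual in weeks: W = A × 52.18/12.
- Mean follow-up past week 96: W/2. Share = (W/2)/(96 + W/2).
- With c = 30/7 = 4.29 weeks, mean follow-up more than 30 days past week 96: (W − c)²/(2W), over the same denominator.

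For A = 12: W = 52.2 and W/2 = 26.1, so 26.1/122.1 = 21.4%. Then (52.2 − 4.29)²/(2 × 52.2) = 22.0, and 22.0/122.1 = 18.0%.

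| A (months) | W (weeks) | Mean weeks past 96 | Share | Mean weeks > 30 days past 96 | Share |
|---|---|---|---|---|---|
| 6 | 26.1 | 13.0 | 12% | 9.1 | 8% |
| 12 | 52.2 | 26.1 | 21% | 22.0 | 18% |
| 18 | 78.3 | 39.1 | 29% | 35.0 | 26% |
| 24 | 104.4 | 52.2 | 35% | 48.0 | 32% |

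The remaining 65% to 88% of adverse event follow-up lies before week 96, where events can be classed.

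**The case against.** **The conflict may be only a translation fault.** The sentence in 9.2 is grammatically damaged. Since 9.1.1 has already defined the term, 9.2 and 12.2.2 may simply mean events meeting that definition, up to the survey. This is a fair reading, and it removes the contradiction in principle. It does not remove the need for a last-dose date after week 96.

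**The safety tables remain separable.** A reader might infer that on-drug and off-drug events cannot be told apart anywhere. The documents do not support that: section 10.1.3 provides what is needed up to week 96. Only later follow-up is affected. Adverse drug reactions can also still be identified after week 96 from the causality field on the survey form, although that field is a judgement and not a record of exposure.

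**Section 9.4.1 is not a third conflicting window.** It covers serious events "from the start of darbepoetin alfa administration to within 30 days after its completion or discontinuation", and might be taken to end adverse event collection at 30 days. It governs only emergency reporting. A shorter urgent-reporting window does not contradict a longer evaluation window. Its effect is that later serious events may be evaluated without being urgently reported.

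**No comparison with the package insert is planned.** Section 9.3 lists side-effect rates only as expected reactions. They are not all-cause adverse event rates, so no loss of comparability can be claimed from them.

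**An on/off-treatment table is ordinary SAP content.** This is true, and its absence from the protocol would be no fault by itself. The list of items collected is fixed in the protocol, and that part of the point stands.

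**The darbepoetin row of the schedule is a figure that is not shown.** The evidence is therefore the item lists in 10.1.3 and 10.1.4 and the form deadlines in 14.1. These agree with each other.

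**Conclusion.** The point holds in two parts. First, 9.1.1, 9.2 and 12.2.2 do not state one adverse event window, and 13.3.3 pools whatever is collected. Second, for patients still treated at week 96, events more than about 30 days after the last recorded dose cannot be assigned to on-drug or off-drug time, because no darbepoetin item is listed at the simultaneous survey.

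The illustrative size is 12% to 35% of adverse event follow-up after week 96, or 8% to 32% counting only time more than 30 days past it, for 6 to 24 months of accrual. These figures rest on assumed accrual length, uniform accrual and no attrition. Deaths and losses would lower them. They are shares of follow-up time, not of events, and they also include time from patients who had already stopped darbepoetin, whose later events can be classed as off drug if they did not restart.

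The consequence is confined to a descriptive secondary safety endpoint in an exploratory observational study. Neither primary endpoint is affected. It is still worth correcting, because missing exposure data cannot be recovered at analysis.

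**What to change.** 1. Reconcile 9.1.1, 9.2 and 12.2.2 to one stated adverse event window, and repair the broken sentence in 9.2.
2. In 13.3.3, tabulate events from first dose to 30 days after the last dose separately from later events up to the simultaneous survey.
3. Add three fields to the 10.1.4 survey form: darbepoetin continued (yes/no), date of last dose, and other ESA used (yes/no). Extend the 14.1 deadline wording to match.

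The cost is wording in a few sections, three fields on a form planned for all patients, and one extra table. Counts in the main safety table will be slightly smaller, because later events move to the second table. No treatment or visit changes.
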